## Background

Patients with major depressive disorder (MDD) and co-morbid chronic pain now have a high risk of not receiving optimal care [1-4]. The burden of co-morbid pain to depression is high for patients in terms of disability, wellbeing, and use of medical care [5]. Complex, integrated collaborative care including active pain management is perhaps better for this population than antidepressants alone, but there is limited evidence. Once such integrated care is available and effective, the added value of an antidepressant over placebo is also under debate. In this trial we aim to evaluate to what extent depressive symptoms improve in patients with MDD with concomitant pain symptoms of both 6–12 weeks and ≥ 12 weeks duration [6]: a) with collaborative care versus an antidepressant alone, and b) with an antidepressant versus placebo within the collaborative care condition.

There is a strong correlation between pain and psychiatric distress reporting [7-11]. Physical symptoms, including several pain symptoms, increase the likelihood of a depressive disorder [12]. Also, many patients with pain symptoms experience a depression [5,13,14], and when the number of pain symptoms increases, the prevalence of depression increases as well [15,16]. Vice versa, when the severity of depression increases, so does the severity of pain complaints [10]. Furthermore, several studies indicate that pain symptoms are common in patients with MDD: the ARTIST trial reports a 69% rate of pain symptoms in primary care patients with depression [17]; in psychiatric clinics in Spain, almost 60% of patients with depression had pain complaints [18]; an international telephone survey in 18,980 patients with MDD showed that 43.4% presented themselves with chronic painful physical conditions [19], with headache, back pain, and limb pain being the most prevalent; the mean prevalence of pain was 65% in a meta analysis of 14 studies [5], and a US telephone survey reported a 65.6% prevalence of chronic pain in depressed persons (N = 5808) [20]. Although a strong correlation has been found between depression and pain, it is not clear if depression causes pain [8], but it is suggested that pain could be a symptom of depression [5,9,21]

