## Methods/Design

### Objectives

The primary objective of this randomized placebo-controlled trial is to establish effectiveness on severity of depression (measured by Patient Health Questionnaire (PHQ-9)) of a closely monitored integrated intervention (TCCCL + duloxetine) for concomitant depression and (sub)chronic pain compared to either TCCCL + placebo and compared to Duloxetine alone.

Secondary objectives of this trial are to establish cost effectiveness in terms of Quality of Adjusted Life Years (QALY) as measured by EuroQol-5 and SF-36 and costs measured by TIC-P; and to establish improvement on pain in terms of Brief Pain inventory (BPI).

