### The study will evaluate the following hypothesis

#### Hypothesis

Combined treatment (TCCCL + Duloxetine) is more effective than mono-treatment (either TCCCL + placebo or Duloxetine alone) in depressive symptom reduction on the PHQ-9 as main outcome for patients with MDD and (sub) chronic pain.

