### Sample size

#### Sample size for severity of depression as primary outcome

In a former RCT on collaborative care performed in the primary care setting, the effect size of a collaborative care intervention versus no such intervention as measured by PHQ-9 was 4.64/7.6 = 0.6 (the SD on the endpoint PHQ-9 varied between 7.0 and 8.3) [104]. In this study, we compare collaborative care plus duloxetine and collaborative care plus placebo versus the monotherapy duloxetine alone, and we compare collaborative care plus duloxetine versus collaborative care plus placebo. To have a minimum power of 80% to detect a standardized difference of 0.5 a minimum of 63 patients per arm is needed, that is 189 completers. In order to anticipate for possible loss to follow up of 20%, 3 × 79 (237) patients will be included [105].

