#### Analysis

Apart from patients that will have to be excluded because of noncompliance as described above, or patients who had to undergo emergency deblinding due to serious medical adverse events, intention to treat analysis will be performed. Multi Level Analysis will be performed which will allow us to correct for variance associated with the different sites in this Multisite RCT. Effect sizes will be estimated in terms of Cohen's d and regression analysis will be performed. Possible confounders such as age, gender, immigrant status, level of education, history of treatment and life events will be included as covariates in the analysis. An independent Helmert analysis will be performed with the following contrasts: Duloxetine alone versus TCCCL + duloxetine and TCCCL + placebo; and then TCCCL + duloxetine versus TCCCL plus placebo.

To assess the cost effectiveness, we will apply a cost-utility analysis. The results will be expressed as cost per QALY. The economic evaluation will be undertaken from a societal perspective. Hence, all relevant effects and costs due to resource utilisation within the healthcare (direct medical costs) and costs due to production losses (productivity costs) will be included.

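### The planned contrasts compare duloxetine alone with the two collaborative care arms pooled, not with combined treatment as the primary objective and hypothesis require

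*Protocol article*

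**What the plan says.** The Objectives section of the Protocol article sets the combined intervention against both other arms: "compared to either TCCCL + placebo and compared to Duloxetine alone". The Hypothesis section says the same: "Combined treatment (TCCCL + Duloxetine) is more effective than mono-treatment (either TCCCL + placebo or Duloxetine alone) in depressive symptom reduction". The Background part of the Abstract names the same two comparators.

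The Analysis section plans a Helmert analysis with two contrasts: "Duloxetine alone versus TCCCL + duloxetine and TCCCL + placebo; and then TCCCL + duloxetine versus TCCCL plus placebo". The Sample size section follows that scheme: "we compare collaborative care plus duloxetine and collaborative care plus placebo versus the monotherapy duloxetine alone", and then the two collaborative care arms against each other.

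The aims at the start of the Background are worded differently: "a) with collaborative care versus an antidepressant alone, and b) with an antidepressant versus placebo within the collaborative care condition".

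On size, the Sample size section states: "To have a minimum power of 80% to detect a standardized difference of 0.5 a minimum of 63 patients per arm is needed". The article gives no significance level and no expected effect of duloxetine over placebo.

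**The concern.** The primary hypothesis has two parts: combined treatment beats TCCCL + placebo, and combined treatment beats duloxetine alone. The second Helmert contrast tests the first part. No planned contrast tests the second part directly.

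The first Helmert contrast is not equivalent to it. It averages the two collaborative care arms, and patients in one of those arms receive no active antidepressant. It therefore mixes the gain from collaborative care with the loss of duloxetine in half of the pooled patients. The better duloxetine works, the smaller the contrast becomes, even when the advantage of combined treatment over duloxetine alone is unchanged. A significant result on it would not by itself show that combined treatment beats duloxetine alone, and a null result would not show that it does not.

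**Working it through.** **Inputs.** From the Sample size section: 63 completers per arm, three equal arms, standardized difference 0.5, power 80%. Assumed: two-sided 5% significance, additive effects of collaborative care (c) and duloxetine (d) in SD units, and a range of values for d.

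**The plan's own figure.** n per arm = 2 × (1.960 + 0.842)² / 0.5² = 62.8, so 63. The stated size is reproduced, which supports the assumed significance level. One-sided 5% would give 50 and two-sided 2.5% would give 77. The 63 is the size for a comparison of two single arms.

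**What each contrast estimates.** Relative to a common reference, the arm means are d (duloxetine alone), c + d (TCCCL + duloxetine) and c (TCCCL + placebo).

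- Pooled contrast: [(c + d) + c]/2 - d = c - d/2
- Contrast within collaborative care: (c + d) - c = d
- Combined treatment minus duloxetine alone: (c + d) - d = c

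The missing comparison equals the pooled contrast plus half of the within-care contrast: (c - d/2) + d/2 = c.

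**Standard errors.** Pooled: √(1/63 + 1/126) = 0.154 SD. Pairwise: √(2/63) = 0.178 SD.

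**Power at c = 0.5 SD.** Power = Φ(effect/SE - 1.96). The direct comparison has 0.5/0.178 = 2.81, hence 80%, whatever d is. For the pooled contrast:

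| d (assumed) | Expected pooled contrast | Ratio to SE | Power |
|---|---|---|---|
| 0 | 0.50 | 3.24 | 90% |
| 0.2 | 0.40 | 2.59 | 74% |
| 0.3 | 0.35 | 2.27 | 62% |
| 0.5 | 0.25 | 1.62 | 37% |

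**Break-even.** The two have equal power when (0.5 - d/2)/0.154 = 0.5/0.178, so 0.5 - d/2 = 0.433 and d is about 0.13 SD. Below that the pooled contrast has more power; above it, less.

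**Two cases where the contrasts disagree.** With c = 0.25 and d = 0.5, the pooled contrast expects 0.25 - 0.25 = 0, although combined treatment is 0.25 SD better than duloxetine alone. With c = 0 and d = 0.5, it expects -0.25, in favour of duloxetine alone, although combined treatment and duloxetine alone do equally well.

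**Joint power of the two pairwise comparisons.** They share the TCCCL + duloxetine arm, so their correlation is (1/63)/(2/63) = 0.5. With 0.5 SD on each, the bivariate normal probability that both are significant is 68.9%, about 69%.

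**The case against.** The strongest reply is that the Helmert set is deliberate. The Background aims, the Sample size section and the Analysis section all point to it, and only the Objectives, the Hypothesis and the Abstract's aim point to the two pairwise comparisons. On that view the defect is loose wording of the hypothesis. Part of this stands: the article does contain two sets of questions, and rewording the hypothesis is a legitimate repair. But the Objectives section carries the labelled primary objective, and the Hypothesis section states the only hypothesis. Even for the first Background aim, the pooled contrast is offset by half of any duloxetine effect.

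A second reply is that little may be lost. The Background calls the added value of an antidepressant within integrated care a matter of debate, so d may be small, and at d = 0 the pooled contrast is both unbiased for c and more powerful. That is correct, and 37% is one scenario, not a forecast. Yet the stated hypothesis itself predicts d above zero within collaborative care.

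A third reply is that the missing comparison can be estimated from the same fitted model, and that positive true values on both Helmert contrasts would imply it. Also true, so the design and data are sound. But this route needs the diluted contrast to succeed, and no section names the derived comparison. The Analysis section mentions Cohen's d and regression without naming any pairwise comparison.

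A reader might infer three stronger points that the article does not support:

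- **That the trial cannot confirm or refute its hypothesis.** One half is tested directly and the other is estimable.
- **That 63 per arm is wrong for a 63 versus 126 contrast.** That contrast is more precise than a pairwise one, and a true 0.5 SD difference on it has 90% power.
- **That the two contrasts inflate the family-wise error rate.** This would need a rule allowing a claim on either contrast, and the article states none.

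**Conclusion.** The concern holds as a mismatch between the primary hypothesis and the planned contrasts. One of the two required comparisons is replaced by a pooled contrast that differs from it by half the duloxetine effect. At c = 0.5 SD the power of the pooled contrast runs from 90% down to 37% as d goes from 0 to 0.5 SD, against a constant 80% for the comparison that the hypothesis names.

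The algebra rests on additivity. The power figures also rest on two-sided 5%, which the article does not state, and on assumed values of d. The mismatch itself rests on none of these, since it is visible from the wording alone. The fault lies in the stated plan, not in the randomised design or the data to be collected.

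**What to change.** Name two primary contrasts, both from the same multilevel model: TCCCL + duloxetine minus duloxetine alone, and TCCCL + duloxetine minus TCCCL + placebo. State that the hypothesis is supported only if both are significant at two-sided 5%; under that rule no alpha split is needed. Report joint power of about 69% at 0.5 SD each beside the 80% per comparison. Keep the pooled Helmert contrast as secondary, and bring the Background aims and the Sample size section into line.

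If the Background aims are the intended ones, reword the Objectives and Hypothesis to match them, and state that the pooled contrast estimates the collaborative care effect less half of the duloxetine effect.

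Either way the change is to wording, with no added patients or data. The first option gives up orthogonality (correlation 0.5 between the two contrasts) and puts a less favourable power figure on record.

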#### Intervention

##### First and second design arm: Duloxetine/placebo plus collaborative care

This intervention contains collaborative care, duloxetine or placebo, and pain medication according to an algorithm. Collaborative care will be provided within a multidisciplinary team comprising of a care-manager, psychiatrist and a physiotherapist. They all will apply treatment simultaneously according to protocol. Only patients in the collaborative care arms will receive treatment of all three specialists. The patients in the Duloxetine alone arm will only receive treatment of the psychiatrist.

The GP of the patient will be informed of the participating of the patient. Also, GP's in the same areas as the mental health centers will receive information about the study and are asked to refer patients if they have the complaints under study. The interventions will be monitored every two weeks and when needed, the doses of medication can be raised according to the algorithm shown in Figures 2 and 3. The minimum duration of the interventions will be 12 weeks. The medication blinding code will be broken after 12 weeks. A maximum of 2 sessions will follow to end the treatment. After this, medication and follow up treatment will be handed over to the GP. In case of treatment response (50% reduction on the initial score), but non-remission, as indicated by a score of > 5 on the PHQ-9 after 12 weeks, the patient will be referred back to the GP with subsequent antidepressant treatment and pain medication advice.

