#### Secondary parameters

Secondary parameter will be the severity of pain symptoms as measured with the total BPI. The BPI has been validated for chronic non-malignant pain [79]. The localization of pain and pain being nociceptive, neuropathic or mixed of nature is assessed at the beginning of the treatment by use of the PAINDETECT questionnaire [74].

In addition to the improvement in the severity of symptoms, the cost utility of the three conditions will be compared to each other. To evaluate the cost utility of each condition, the difference in direct medical costs per patient receiving collaborative care and duloxetine, collaborative care and placebo, or Duloxetine alone is related to the difference in terms of Quality Adjusted Life Years (QALY) gained. This will yield a cost per QALY estimate. These data will be collected with the Trimbos/iMTA questionnaire for Costs associated with Psychiatric Illness (TiC-P), a measure commonly applied in economic evaluations of treatment in mental care [89,90]. The TiC-P measures direct costs of medical treatment such as the number of contacts with the general practitioner and multiple other care providers (e.g. paramedics and medical specialists) during the last three months. Medication use is measured during the last four weeks. Also, the TiC-P includes a short form of the Health and Labor questionnaire (HLQ) for collecting data on productivity losses [91], the SF-HLQ. It measures productivity loss by collecting data on absence from work, reduced efficiency at work and difficulties with job performance [92].

The EuroQoL (EQ-5D) [93] and the Short Form-36 (SF-36) [94] will be used to assess quality of life. Both are validated instruments for the measurement of general health-related quality of life. The EQ-5D measures quality of life on five dimensions, namely mobility, self-care, usual activities, pain/discomfort and anxiety depression.

3. *Additional outcome measures*

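### The economic evaluation is labelled societal but counts only health care and productivity costs, which is likely to understate the incremental cost of collaborative care against duloxetine alone

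*Protocol article*

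**What the plan says.** The Analysis section of the protocol article announces a cost-utility analysis expressed as cost per QALY and says: "The economic evaluation will be undertaken from a societal perspective". The sentence that follows opens with *Hence* and sets out the scope: "costs due to resource utilisation within the healthcare (direct medical costs) and costs due to production losses (productivity costs) will be included". No other cost category is named.

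The Secondary parameters section describes the measurement. For care use: "The TiC-P measures direct costs of medical treatment such as the number of contacts with the general practitioner and multiple other care providers". For the short Health and Labor questionnaire (SF-HLQ) inside the TiC-P: "It measures productivity loss by collecting data on absence from work, reduced efficiency at work and difficulties with job performance". Medication use is also recorded. Patient travel, unpaid patient time and informal care are not mentioned. The same section defines cost utility on a narrower basis still, relating "the difference in direct medical costs per patient" to the QALYs gained.

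On the treatment load, the section on the first and second design arms says: "Only patients in the collaborative care arms will receive treatment of all three specialists". It adds: "The patients in the Duloxetine alone arm will only receive treatment of the psychiatrist".

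**The concern.** A societal perspective is broader than what the payer and the employer bear. It also covers what falls on patients and families, such as travel, time given up for treatment and informal care. The article states the broad perspective and then defines it by two categories that leave these costs out.

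The gap would matter little if the omitted costs were equal in all arms. They are not equal by design, because the collaborative care arms require more contacts and more work at home. Leaving out a cost that rises with treatment contacts makes the more contact-heavy arm look cheaper, relative to duloxetine alone, than a societal analysis would.

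Cost effectiveness is a secondary objective (Objectives). The Dissemination of results section says the study will establish it for the collaborative care model as a basis for implementation. A reader who takes the societal label at face value would think that the patients' own costs are in the ratio.

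**Working it through.** **Stated perspective against listed costs**

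| Source in the protocol article | Direct medical | Productivity | Patient travel and unpaid time | Informal care |
|---|---|---|---|---|
| Societal perspective (the label) | yes | yes | yes | yes |
| Analysis, categories listed | yes | yes | not named | not named |
| Secondary parameters, TiC-P as described | yes | yes (SF-HLQ) | not named | not named |
| Secondary parameters, cost-utility definition | yes | no | no | no |

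The article therefore holds three different scopes: the label, the two-category list and the direct-medical-only definition.

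**Planned patient burden by arm**

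| Component | Collaborative care (both arms) | Duloxetine alone |
|---|---|---|
| Psychiatrist | yes | yes |
| Care-manager, with problem solving treatment | yes | no |
| Physiotherapist | yes | no |
| Self-help manual with exercises | yes | no |
| Physiotherapy exercises at home | yes | no |

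Sources: intervention items 4, 5 and 8, the section on the first and second design arms, and the section on the third design arm. The two collaborative care arms share the same planned contacts, so omitted visit costs largely cancel between them. Against duloxetine alone they do not.

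**Size**

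The article states no economic figure, so there is none to reproduce. The shift can only be written as a formula:

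- omitted cost per patient = V × c
- shift in cost per QALY = V × c / ΔQ

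Here V is the number of extra visits under collaborative care, c the travel and time cost per visit, and ΔQ the QALY gain over duloxetine alone. None of the three is in the document. The following ranges are assumptions: V from 6 to 24, c from EUR 5 to 30, ΔQ from 0.02 to 0.10.

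| V × c | Omitted cost per patient | ΔQ = 0.10 | ΔQ = 0.05 | ΔQ = 0.02 |
|---|---|---|---|---|
| 6 × 5 | EUR 30 | 300 | 600 | 1,500 |
| 12 × 15 | EUR 180 | 1,800 | 3,600 | 9,000 |
| 24 × 30 | EUR 720 | 7,200 | 14,400 | 36,000 |

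The last three columns are EUR per QALY. The middle case is 12 × 15 = 180 and 180 / 0.05 = 3,600. Manual and home-exercise time are not in these figures and would add to them. The formula presumes a positive ΔQ; with no gain or a loss, the ratio does not have this meaning.

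**Can visit costs be recovered?**

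The TiC-P asks about contacts over the last three months (Secondary parameters), and measurements fall at 3, 6, 9 and 12 months (Data collection). Four windows of three months cover the follow-up year. The Case Registration Form is a weaker source: it is described as listing the steps of care-manager and psychiatrist appointments. It is not said to yield visit counts, and physiotherapists are not mentioned.

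**The case against.** The strongest defence is that this is a condensed article. Itemised costs and unit prices usually sit in a fuller plan, and the TiC-P content is given only by way of example. That defends the absence of item lists, but not the mismatch: the article itself states which categories follow from the societal perspective, and they are narrower than the label.

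A reader might go further and infer that the cost per QALY is shown to be biased in favour of collaborative care. The document does not support that, for four reasons:

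- **Scope.** Only comparisons with duloxetine alone are affected to any extent.
- **Direction over 12 months.** The interventions last at least 12 weeks, with at most two closing sessions, while costs run for a year. The consultation letter, given only with collaborative care, advises against repeated diagnostic procedures and hospital admission, which could lower later patient costs. It also advises regular GP check-ups every 6 weeks, which could raise them. Patients on duloxetine alone may travel to more outside care, and informal care could go either way.
- **Overlap.** Working hours lost to appointments may already enter through the SF-HLQ as absence. Treatment time is therefore not wholly uncounted.
- **Size.** Every input is assumed, and the resulting range is too wide to show that the effect is material.

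These points stand. They limit the conclusion to a likely understatement of unknown size, and they do not restore agreement between the label and the listed costs.

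It can also be said that the conflict between the Secondary parameters and Analysis sections over productivity costs is the firmer defect. It is, but settling it in favour of the Analysis section would still leave a two-category analysis called societal.

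**Conclusion.** The concern holds in a limited form. The Analysis section claims a societal perspective and defines it as health care plus productivity costs, so patient travel and unpaid time are left out. Because planned contacts are heavier under collaborative care, the omission is likely, though not certain, to understate its incremental cost against duloxetine alone. The comparison of collaborative care with duloxetine against collaborative care with placebo is largely unaffected.

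The amount cannot be computed from the document. The illustrative EUR 300 to 36,000 per QALY rests entirely on the assumed visit numbers, unit costs and QALY gain, and shows only that the effect could be trivial or material. This is a minor point about a secondary objective. It does not touch the primary PHQ-9 analysis.

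**What to change.** Choose one of two routes in the Analysis section.

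1. **Widen the costs.** Add patient travel and visit-time costs, computed as TiC-P contact counts at 3, 6, 9 and 12 months times standard unit prices. Confirm that care-manager and physiotherapist contacts are among those counted. State how working time already recorded as absence by the SF-HLQ is kept from being counted twice. State openly that informal care and home-exercise time are not captured, since visit counts cannot supply them.
2. **Narrow the label.** Rename the perspective 'health care and productivity' and limit the cost-per-QALY conclusion to it.

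Under either route, reconcile the cost-utility definition in Secondary parameters, now direct medical costs only, with the definition chosen.

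The first route costs some extra analysis and probably a less favourable ratio for collaborative care against duloxetine alone. It needs no new questionnaire item, provided the contact counts are complete. The second costs only wording and gives up the societal claim.
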